### Allocation

For randomization, the “blockrand” function in R 4.1.0 (Ross Ihaka, Robert Gentlemen, New Zealand) will be employed to generate random sequences. We will first divide the seven communities into the compulsory randomization cluster (three communities) and patient preference cluster (four communities) via cluster randomization. Then, we will generate a random sequence with a block size of four to randomly assign the patients into the HSM or control group in a 1:1 ratio in a compulsory or voluntary manner.

The random sequence will be concealed using scratch cards printed with a random number corresponding to the participation order. Until the coating is scratched, neither the patients nor the investigators will have knowledge about the group assignments. An independent investigator who is not involved in the implementation and follow-up of this study will generate and save the randomization sequence and prepare scratch cards. Although blinding is impossible for the patients and physicians, the data analysts will not be aware of the treatment allocation.

Patients who have a clear preference may be free to choose to enter the HSM or control group, with an allocation ratio of 1:1. Hence, when either nonrandomized group is full, the remaining patients will have to enter another nonrandomized group.

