### Data collection and management

At each study site (i.e., community healthcare center), a community physician will be responsible for patient recruitment, HSM training, and outcome assessment; a clinical coordinator will be responsible for regular contact with patients with regard to follow-up visits, recording basic information, and distributing moxibustion materials. Prior to the start of the trial, all investigators will be trained on the standard operating procedure and complete simulated baseline and follow-up visits before being allowed to conduct the investigation.

Raw data will be recorded on paper-based case report forms stored in a lockbox at each study site. Electronic data entry will be performed at any interim analysis and at the end of follow-up by an approach in which two clinical coordinators independently and repeatedly enter the data into standardized forms created in Microsoft Access (Microsoft Corporation, USA). The electronic data set will be anonymized and kept confidential. Only the blinded data analyst can access the data set.

The following trial committees will be established for quality assurance: a steering committee consisting of acupuncturists, cardiologists, methodologists, and statisticians and responsible for study design, maintenance of the quality of study conduct, safety monitoring, and study publication; a coordinating center consisting of the principal coordinating investigator and the coordinating investigators of each community and responsible for the overall study conduct, interactions with the communities and sponsors, and reporting trial advancements to the steering committee; an independent endpoint adjudication committee consisting of cardiologists and acupuncturists and responsible for reviewing the assessment of the primary endpoint and subjective outcomes; and an independent data-monitoring committee consisting of acupuncturists, cardiologists, methodologists, and statisticians for monitoring the data management, directing the interim analysis, and deciding whether to continue the trial based on the results of safety, efficacy, and compliance assessment.

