### Sample size estimation

The primary purpose of sample size estimation is to meet the need for statistical power for primary outcome comparison between randomized groups. Based on the results of our previous nonrandomized studies (not yet published) and expert opinion, we assume that the SBP in the HSM group will be on average 5 mmHg lower than that in the control group after 6 months of HSM treatment, with a common standard deviation of 8 mmHg between the groups. With a type I error probability “α” of 0.05 and type II error probability “β” of 0.20 and the allowance of a 20% attrition rate, a minimum of 51 patients in either the randomized HSM or control group is needed, as calculated by the following formula for the superiority design [22]:
$$ N=2\times {\left(\frac{Z_{1-\frac{\alpha }{2}}+{Z}_{1-\beta }}{\upmu_1-{\upmu}_2}\right)}^2\times {s}^2 $$

We ultimately decided to enlarge the total sample size to 400, as a sample of this size can be supported by funding. We administered a small preference survey to 100 patients at the study sites, which showed that the ratio of patients with a preference (a strong willingness to enter the HSM or control group) to those without a preference (accept the randomization) was approximately 6:1. Considering the feasibility of the study and the need for confounder adjustment, we established a sample size for the voluntary randomization group of 40 (20 per group) such that the size of the preference selection (nonrandomized) group would be 240 (120 per group). The remaining 120 patients will be entered into the compulsory randomization group (60 per group). Figure 1 illustrates the sample size scheme for each arm.

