### Statistical analysis

Data analysis of the primary outcome will be based on the full analysis set constructed by the intention-to-treat principle, whereby patients will remain in their original group regardless of contamination. The per-protocol set will also be analyzed by sensitivity analysis for the primary outcome to evaluate whether contamination impacts the direction of the effect. The secondary outcomes will also be compared based on the per-protocol set. The need to impute missing values will be determined by the proportion of and reasons for missing data. If imputation is necessary, appropriate methods, such as the last observation carried forward, “best-worst-case” scenario and multiple imputation regression modeling, will be chosen according to the distribution of the missing values.

Data analysis will be conducted separately for the randomized and nonrandomized groups, and consistency of effect directions between the two sets of analyses will be evaluated. For the randomized groups, repeated-measures analysis of variance will be employed for the continuous variables measured each month; QoL and symptom scale scores will be compared by *t* tests, and categorical variables will be compared by chi-square tests. These analyses will not be adjusted for covariates unless there are factors that are significantly unbalanced at baseline. For nonrandomized groups, we will utilize repeated-measures ANOVA, linear mixed models, and logistic regression models depending on the data distribution; potential confounders will be adjusted for, including age, body mass index (BMI), baseline SBP, duration of hypertension, type of antihypertensive regimen, diabetes, dyslipidemia, smoking, and alcohol consumption. The between-group difference will be measured by the mean differences for continuous outcomes (i.e., changes in SBP, DBP, dosage of antihypertensive drug, QoL, and hypertensive symptom scores) and the risk ratios (RRs) for binary outcomes (i.e., the response to treatment and incidence of new-onset cardiovascular events).

We are also interested in whether there are different blood pressure lowering effects between HSM regimens with different parameters, which will be explored by the following subgroup analyses with prespecified effect directions based on our clinical experience:

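### The adjustment set for the 240-patient nonrandomized HSM v control comparison names nine patient-level factors and no community term, although arm choice and SBP change could both vary across the four communities.

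*Protocol article*

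**What the plan says.** All references are to the protocol article.

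- **Allocation** fixes where these patients come from: "We will first divide the seven communities into the compulsory randomization cluster (three communities) and patient preference cluster (four communities) via cluster randomization". Within the preference cluster, "Patients who have a clear preference may be free to choose to enter the HSM or control group, with an allocation ratio of 1:1". Once one nonrandomized group is full, later patients go to the other. No quota per community is stated.
- **Sample size estimation** sets the nonrandomized comparison at 240 patients, 120 per group.
- **Data collection and management** says that at each site "a community physician will be responsible for patient recruitment, HSM training, and outcome assessment". Under Outcomes, a physician also decides at each visit whether the drug regimen changes.
- **Statistical analysis** offers repeated-measures ANOVA, linear mixed models or logistic regression for these groups, chosen by data distribution, and says that "potential confounders will be adjusted for, including age, body mass index (BMI), baseline SBP, duration of hypertension, type of antihypertensive regimen, diabetes, dyslipidemia, smoking, and" one more, drinking. Community appears nowhere in that section as a covariate, stratum or random effect.
- The same section compares effect directions between the randomized and nonrandomized analyses. The Discussion expects agreement between them to make the results more reliable.

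**The concern.** In a comparison based on choice, a factor confounds if it influences both the arm entered and the outcome. Community could do both here. The physician who presents HSM to patients in a community also trains them and assesses their outcomes there, and nothing balances HSM against control within a community. The overall cap could even add to the imbalance: if communities recruit at different speeds, those recruiting late feed mainly the arm still open.

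The stated adjustment set addresses patient characteristics and not this route. Baseline SBP and regimen type would absorb part of any site difference, but not differences that arise during follow-up. At stake are the size and confidence interval of the supporting estimate, which draws on 240 of the trial's 400 patients.

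**Working it through.** **Inputs from the protocol article.** "With a type I error probability “α” of 0.05 and type II error probability “β” of 0.20"; effect: "the SBP in the HSM group will be on average 5 mmHg lower than that in the control group"; SD: "with a common standard deviation of 8 mmHg between the groups"; attrition and size: "the allowance of a 20% attrition rate, a minimum of 51 patients in either the randomized HSM or control group is needed".

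**The plan's own figure.** n = 2 × ((1.96 + 0.8416)/5)² × 8² = 40.19 per group. Then 40.19/0.80 = 50.2, rounded up to 51, so the stated minimum reproduces. The arm sizes also agree: 40 × 6 = 240, and 240 + 40 + 120 = 400.

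**Assumptions (not in the documents).** Four communities of 60; total SD 8, so variance 64; community ICC 0.05 unless stated, meaning the part left after the nine covariates; HSM uptake by community averaging 50%; no true effect.

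**Variance without a community term.** Let d be a community's share of the HSM arm minus its share of the control arm.

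- Community variance = 64 × 0.05 × Σd² = 3.2 × Σd²
- Individual variance = 2 × 64 × 0.95/120 = 1.013
- Variance the model reports ≈ 2 × 64/120 = 1.067 (SE 1.03)

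At 30/40/60/70% uptake, d = −0.2, −0.1, 0.1, 0.2 and Σd² = 0.10. True variance = 0.32 + 1.013 = 1.333; the ratio to 1.067 is 1.25; the two-sided false-positive rate is 2 × (1 − Φ(1.96/√1.25)) ≈ 8%.

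| Uptake | Σd² | True variance | Ratio | False positives, formula | Simulated (20,000 runs) |
|---|---|---|---|---|---|
| 50% in all | 0 | 1.013 | 0.95 | 4.4% | 4.4% |
| 30/40/60/70% | 0.10 | 1.333 | 1.25 | 8.0% | 8.0% |
| 25/40/60/75% | 0.145 | 1.477 | 1.38 | 9.6% | 10.0% |
| 20/40/60/80% | 0.20 | 1.653 | 1.55 | 11.5% | 11.6% |
| 20/20/80/80% | 0.36 | 2.165 | 2.03 | 16.9% | 17.0% |

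With community as a fixed effect, the simulated rate is 5.0–5.3%. At 25/40/60/75% the true SE is √1.477 = 1.22 mmHg against 1.03 reported. Over ICC 0.01 to 0.10 at that uptake, the rate without community runs from 5.8% to 14.5%.

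**The same point as a bias.** Suppose SBP change differs by 4 mmHg from best to worst community in equal steps (0, −1.33, −2.67, −4), with uptake 30/40/60/70%. The spurious effect is Σ d × difference = 0 + 0.133 − 0.267 − 0.8 = −0.93 mmHg. A 2 mmHg range with 40/45/55/60% uptake gives −0.23; a 6 mmHg range with 20/40/60/80% gives −2.0. The sign could equally be the reverse. A community fixed effect brings each to zero.

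**Price of the fixed effect.** SE = √(64 × (1 − ICC)/Σ m·p(1 − p)), with m patients per community and uptake p.

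- 30/40/60/70%, ICC 0.05: √(60.8/54) = 1.06 mmHg
- 20/20/80/80%, ICC 0.01, 240 patients: √(63.36/38.4) = 1.28 mmHg; power for 5 mmHg = Φ(5/1.28 − 1.96) ≈ 97%
- The same case with 20% attrition (48 per community): √(63.36/30.72) = 1.44 mmHg; power ≈ 94%

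**The case against.** The strongest reply has five parts.

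1. *The list is open.* The word *including* leaves room for more, a linear mixed model could carry a community term, and a condensed article may leave the full covariate list to an analysis plan. This stands to the extent that a reader may not infer that community was deliberately excluded, or that the plan commits to treating patients as independent. It does not remove the point: the article publishes a specific set, and that set can be improved on its own terms.
2. *Site differences are not shown.* A reader might infer that drug adjustment and measurement are known to vary by site. The documents do not say so. They describe a uniform monitor, training on a standard procedure with simulated visits, and independent review of the primary endpoint assessment. That the recruiting physician is also the one who adjusts drugs is a reasonable reading, not an explicit statement.
3. *The numbers rest on assumed ICC and uptake.* True. They show a range, not an estimate.
4. *The plan compares directions, not significance.* This largely stands. With a true 5 mmHg effect and SE 1.22, a reversed sign has probability of about 0.002% (z = 4.1). Even a 2.0 mmHg bias against HSM leaves 3 mmHg in the same direction. It would overreach to say that the omission undermines the direction check when the effect is near the planned size.
5. *A community term in every model suits rare events poorly.* This stands for new-onset cardiovascular events, and the fix is limited accordingly.

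**Conclusion.** The point holds as a conditional weakness in a supporting analysis. Bias and a too-small standard error need uptake and SBP change both to differ by community; the documents give figures for neither. If both do, the false-positive rate at ICC 0.05 is about 8% to 17% over the uneven-uptake scenarios, against about 5% with a community term. If uptake is equal, the unadjusted test is slightly conservative.

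A reader might extend the concern to the primary comparison. The documents do not support that: allocation there is random among individual patients, so community is not systematically tied to arm. With 64 completers per arm ((60 + 20) × 0.8), power is 93.9% ignoring community and 94.9% after removing an ICC of 0.05. What is gained is a better-founded size and interval for the nonrandomized estimate. The change is worth making, but the trial's main conclusion does not depend on it.

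**What to change.** In the Statistical analysis section, add community (four levels, fixed effect) to the listed adjustment factors for the nonrandomized comparisons of continuous outcomes and treatment response. HSM and control patients are then compared within the same community. A fixed effect is preferable to a random intercept because four communities are too few to estimate a between-community variance well. For new-onset cardiovascular events, include it only if event numbers allow. Report the number of patients in each arm by community, so that readers can see how uneven uptake was.

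The cost is one line of text, no new data and 3 degrees of freedom. If uptake is uneven, the interval widens somewhat: with all 240 patients the SE goes from about 1.03 to 1.1–1.3 mmHg. In the scenarios examined, power for 5 mmHg stays at about 97% or more with 240 patients and about 94% or more after 20% attrition.

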### Visit schedule

Patients will attend a baseline visit and 6 monthly follow-up visits. The follow-up visits will be scheduled every 30 ± 3 days. If a patient does not complete a follow-up visit within the scheduled period for any reason, we will not collect follow-up data for that time period, and the data for that visit will be considered missing. Patients who fail to attend three consecutive follow-up visits within the scheduled time frame will be excluded from the study. At the baseline visit, we will collect information about demographics, comorbidities, medication history, anthropometric measurements (blood pressure, heart rate, height, and weight), and QoL and hypertensive symptom scales. At each follow-up visit, we will record blood pressure, heart rate, new-onset disease or disease progression, treatment and expenses for the month, and AE data. As a basis for patient compliance judgment and subgroup analysis, we will also record the details of HSM, including the actual dosage, frequency, acupoints, and heat-sensitized sensations at each follow-up visit. QoL and hypertensive symptoms will be assessed at the 3- and 6-month follow-ups. The detailed visit schedule is presented in Fig. 2.

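### QoL and symptom scores in the randomized arms are to be compared by plain t tests although both are measured at baseline; a prespecified baseline-adjusted model would be more precise, and own-baseline adjustment in the preference arms should be stated

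*Protocol article*

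**What the plan says.** All references are to the protocol article.

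**Randomized arms.** Under Statistical analysis, outcomes measured monthly go to repeated-measures ANOVA, while "QoL and symptom scale scores will be compared by" t tests. The same paragraph rules out covariate adjustment unless some factor differs significantly between the arms at baseline. It does not say whether the t test is applied to month-6 scores or to changes. The effect measure is a mean difference in "changes in SBP, DBP, dosage of antihypertensive drug, QoL, and hypertensive symptom scores".

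**Preference arms.** "Data analysis will be conducted separately for the randomized and nonrandomized groups". "For nonrandomized groups, we will utilize repeated-measures ANOVA, linear mixed models, and logistic regression models depending on the data distribution"; the adjustment sentence reads "potential confounders will be adjusted for, including age, body mass index (BMI), baseline SBP, duration of hypertension", and the list ends with "type of antihypertensive regimen, diabetes, dyslipidemia, smoking, and alcohol consumption". Baseline SBP is the only baseline outcome value named. Regimen type is listed; baseline dosage is not. The list is introduced as non-exhaustive.

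**Baseline data.** Visit schedule records medication history, "anthropometric measurements (blood pressure, heart rate, height, and weight), and QoL and hypertensive symptom scales".

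**Selection.** Under Allocation, "Patients who have a clear preference may be free to choose to enter the HSM or control group", subject to a 1:1 cap: once one nonrandomized group is full, later patients go to the other.

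**The concern.** A patient's baseline QoL or symptom score is usually the best single predictor of the later score. A t test on month-6 scores ignores it. A t test on changes subtracts all of it, which over-corrects whenever the correlation is below 1. Regression on the baseline uses the right share.

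Making adjustment depend on a baseline significance test misses the reason to adjust. In randomized arms any imbalance is chance, and the gain comes from the correlation with the outcome, not from the size of the imbalance. The rule also leaves the analysis model unknown until the baseline data have been tested.

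In the preference arms the issue is confounding. Patients choose their treatment, so the arms may differ at baseline on the outcome itself, and five change outcomes share a list that names only SBP's baseline. The plan compares effect directions between the randomized and nonrandomized sets, and the Discussion treats agreement as added reliability. A baseline artefact could create or hide such agreement for DBP, QoL, symptoms or dosage.

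**Working it through.** The article gives no figure for this point. Its one sample-size calculation is for SBP and reproduces: 2 × ((1.960 + 0.842) × 8/5)² = 40.19; 40.19/0.8 = 50.23, rounded up to 51 per group.

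**1. Randomized arms: power for QoL or symptom scores**

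From Sample size estimation: 60 compulsory + 20 voluntary = 80 per arm; less 20% attrition, 64. Assumed, because the article gives neither: a true effect of 0.5 SD and a baseline to month-6 correlation ρ. Two-sided α is 0.05.

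In units of the score's SD, the SD that governs the comparison is:
- month-6 t test: 1
- change-score t test: √(2(1 − ρ))
- month-6 score regressed on arm and baseline: √(1 − ρ²)

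Noncentrality = 0.5 / (SD × √(2/64)) = 2.828 / SD.

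| ρ | Month-6 t test | Change t test | Baseline-adjusted |
|---|---|---|---|
| 0.3 | SD 1, power 80% | SD 1.183, power 66% | SD 0.954, power 84% |
| 0.5 | SD 1, power 80% | SD 1, power 80% | SD 0.866, power 90% |

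At ρ = 0.5 the variance falls by ρ² = 25%. The adjusted model is ahead of both t tests in each row.

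**2. Preference arms: what own-baseline adjustment does when HSM has no effect**

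Assumed: 96 completers per arm (120 less 20%), ρ = 0.5, and HSM choosers starting 0.3 SD worse.

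*(a) Both arms regress to a common mean.* The change-score bias is (1 − ρ) × gap = 0.5 × 0.3 = 0.15 SD in favour of HSM. SE = 1 × √(2/96) = 0.144, so z shifts by 1.04 and the nominal 5% test rejects about 18% of the time. In simulation, adding the outcome's own baseline returns rejection to about 5%.

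*(b) The group difference is stable over time.* The change score is unbiased and rejects about 5%. Own-baseline adjustment now shows a false 0.15 SD effect against HSM. Its SE is 0.866 × √(2/96) = 0.125, a z shift of 1.2, and simulation gives rejection of roughly 21% to 23%.

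*(c) Baseline SBP as a stand-in, under (a).* Simulated with 120 per arm and an SBP gap in proportion to its correlation with the outcome's baseline. At ρ = 0.5 and gap 0.3 SD, adjusting for SBP alone leaves a bias of 0.147 SD (rejection 21%) if that correlation is 0.2, and 0.094 SD (11%) if it is 0.6. Over gaps of 0.2 to 0.5 SD and ρ of 0.5 or 0.7, rejection runs from about 8% to 46%. With no gap there is no bias under any model.

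**The case against.** A reader might infer that DBP, QoL, symptoms and dosage in the preference arms will definitely go unadjusted for their own baselines, and that a false HSM benefit will follow. The article does not support this:

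- The confounder list is open, and no sentence excludes own-baseline adjustment. A fuller protocol or SAP may name more covariates.
- Nothing in the article says that patients with worse symptoms or QoL choose HSM. If they start better, the common-mean bias masks a benefit; if the arms start equal, there is none. The 1:1 cap also means that allocation is not purely by choice, which would dilute a preference-driven gap.
- Baseline SBP is a partial proxy for DBP, and regimen type for dosage. In (c), a correlation of 0.6 with SBP removed about a third of the bias.
- Own-baseline adjustment is not automatically right in self-selected groups, as (b) shows.

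All four points stand, and they reduce the preference-arm part to a conditional, secondary suggestion.

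Against the randomized part, one can say that the t test is valid, that these are secondary outcomes on which the trial was not sized, and that the plan already allows adjustment after a significant imbalance. The first two are true: randomization protects the t test from bias, and the loss is one of precision. The third does not help. The allowance depends on a baseline test and will seldom operate in randomized arms, whereas the gain from adjustment does not depend on imbalance. Nor is this a detail left to an SAP, because the article itself fixes the t test and the adjustment rule.

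**Conclusion.** The point holds as an improvement to the secondary analyses. For randomized QoL and symptom scores, the stated t test with adjustment conditional on significant imbalance discards baseline information already collected. Under the assumed 64 completers per arm and 0.5 SD effect, a baseline-adjusted model gains about 4 to 10 percentage points of power over a month-6 t test, and about 18 to 10 points over a change-score t test, at correlations of 0.3 and 0.5 respectively. Effect size and correlation are not in the article. The completer count is also an assumption: secondary outcomes are to be compared in the per-protocol set, which may be smaller.

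For the preference arms, the supported statement is only that own-baseline adjustment is not stated for four of the five continuous change outcomes. The size and direction of any bias cannot be fixed from the article, and either analysis can mislead, depending on whether the arms share a common mean. Agreement in direction on these outcomes is therefore weak corroboration until both analyses have been seen. The primary randomized SBP comparison is not affected, and SBP's own baseline is already listed for the preference arms.

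**What to change.** In Statistical analysis:

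1. **Randomized arms.** Replace the t tests for the EQ-5D-5L index, the EQ-5D visual analog scale and the symptom score by a linear model of the month-6 score on arm and the baseline value of that score. Prespecify it for all three, regardless of any baseline significance test.
2. **Preference arms.** Add to the confounder list the baseline value of the outcome being analysed (DBP, EQ-5D-5L index and visual analog scale, symptom score, drug dosage), keeping baseline SBP. Report alongside, as a sensitivity check, the change analysis without the outcome's own baseline. Treat consistency of direction as corroboration only where the two agree.

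The cost is a few sentences of analysis wording and one degree of freedom per model, plus one extra reported analysis per outcome in the preference arms. Baseline DBP, QoL and symptom scores are already scheduled. Baseline dosage should be obtainable from the medication history, since the planned dosage-change outcome needs it anyway. The wording should be settled before the outcome data are examined.

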A high degree of heat-sensitized sensation is expected to be associated with better efficacy than a low degree. A scale developed in-house will be used to measure the degree of heat-sensitized sensation. The scale includes four dimensions (depth/range/distance [not available for three systemic reactions], intensity, frequency, and comfort) for 12 sensations (Additional file 2). Each dimension can receive a score of 0 to 5 points. A patient whose total score in the four dimensions for any sensation is ≥ 60% (i.e., 15 points) will be considered to have achieved a high degree of heat-sensitized sensation. This scale was tested in a sample of 64 patients and showed good reliability and validity—the Cronbach alpha coefficient was 0.892, and the factor loadings for all items were > 0.6.HSM ≥ 4 times per week is expected to be associated with better efficacy than HSM < 4 times per week.Heat-sensitized sensations at both the main and matching acupoints are expected to be associated with better efficacy than heat-sensitized sensations at only the main acupoint.The development of nonthermal sensation (the last 7 moxibustion sensations on the scale) is expected to be associated with better efficacy than the development of only thermal sensation.

In addition, subgroup analyses comparing patients who underwent compulsory and voluntary randomization will be carried out to validate the impact of patient preference on the effects.

If the HSM group shows a better response to treatment than the control group, we will perform an economic evaluation in which the cost-effectiveness ratio and incremental cost-effectiveness ratio will be used as indicators. If a better response to treatment is associated with the frequency of HSM, the balance between the costs of moxibustion materials and outcomes will be explored. A cost-effectiveness acceptability curve will be applied to visualize information about uncertainty in the cost-effectiveness analysis.

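### The cut-off for a high degree of heat-sensitized sensation equates 60% with 15 points, but on the scale as described 60% is 12 points and 15 points is 75%

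*Protocol article*

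**What the plan says.** The Statistical analysis section of the protocol article lists subgroup analyses with a direction fixed in advance. The first states: "A high degree of heat-sensitized sensation is expected to be associated with better efficacy than a low degree". Degree is measured with an in-house scale, described as follows: "The scale includes four dimensions (depth/range/distance [not available for three systemic reactions], intensity, frequency, and comfort) for 12 sensations". On scoring, the article says: "Each dimension can receive a score of 0 to 5 points". The classification rule begins "A patient whose total score in the four dimensions for any sensation is" and sets the threshold at or above "60% (i.e., 15 points) will be considered to have achieved a high degree of heat-sensitized sensation".

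The scale itself is in Additional file 2, which is not among the documents at hand. The article gives no other maximum, weighting or rescaling, and no separate cut-off for the systemic reactions.

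**The concern.** The rule gives one threshold in two forms, a percentage and a number of points, and on the scale described in the same paragraph they are different thresholds. The sentence also leaves unclear what happens to the three systemic reactions, for which the first dimension is "not available for three systemic reactions".

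What is at stake is who falls into the high and low groups of a subgroup analysis whose direction has been declared. Eligibility already requires patients in the HSM group to show at least one heat-sensitized sensation around a main acupoint. Presence alone therefore cannot separate them, and the cut-off does the sorting. With two cut-offs in the text, the choice between them stays open until the analysis. Keeping the analyst unaware of treatment allocation does not close it, because this contrast is between patients with different sensation scores.

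**Working it through.** **Inputs (all from the Statistical analysis section)**
- Dimensions per sensation: 4 (depth/range/distance counted as one, plus intensity, frequency and comfort).
- Dimensions for the three systemic reactions: 3.
- Score per dimension: 0 to 5.
- Cut-off: at least 60%, equated with 15 points.
- Unit: the total for any single sensation, not a sum over the 12 sensations.

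**Step 1: try to reproduce the stated 15 points.** Maximum = dimensions × 5; cut-off = 0.60 × maximum.
- Four dimensions: maximum 4 × 5 = 20; 0.60 × 20 = 12 points. The stated 15 is 15/20 = 75%.
- Not reproduced.

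**Step 2: look for a reading that would give 15.**

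| Reading | Maximum | 60% cut-off | 15 points equals |
|---|---|---|---|
| Four dimensions, as described | 20 | 12 | 75% |
| Depth, range and distance scored separately (six dimensions) | 30 | 18 | 50% |
| Four dimensions scored 1 to 5, 60% of the range above the minimum of 4 | 20 | 4 + 0.60 × 16 = 13.6 | 11/16 = 69% of the range |
| Five dimensions | 25 | 15 | 60% |

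Only a maximum of 15/0.60 = 25 works. That needs five dimensions of 0 to 5, which the article does not describe.

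**Step 3: systemic reactions.** Maximum 3 × 5 = 15. Fifteen points is 15/15 = 100%. If 60% is taken of their own attainable maximum, the cut-off is 0.60 × 15 = 9. If it is taken of the four-dimension maximum, the cut-off is 12. The article states neither.

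**Step 4: who is classified differently.** The rule is met by any one sensation. The versions therefore disagree only for a patient who reaches the 60% cut-off on at least one sensation and 15 points on none. A patient with 15 or more on any sensation is high under both.

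**Step 5: how far apart the cut-offs are.** With four dimensions there are 6⁴ = 1296 possible score patterns for one sensation. Of these, 435 (33.6%) reach 12 points and 126 (9.7%) reach 15, so 435 − 126 = 309 (23.8%) lie between. This counts equally weighted patterns for a single sensation and does not forecast patients. It shows only that the cut-offs are not near-equivalent.

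**The case against.** The case on the other side accepts the mismatch and argues that its consequences are small and partly unknown. Most of that stands.

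- A reader might infer that every patient with a best score of 12 to 14, or of 9 to 14 on a systemic reaction, changes group. The any-sensation rule does not support this. Someone with 9 to 14 on a systemic reaction and 15 or more elsewhere is high either way. So is someone whose best four-dimension score is 12 to 14 but who has a full 15 on a systemic reaction.
- A reader might also infer that patients whose chief sensation is a systemic reaction could hardly ever be classed as high. The article defines no chief sensation, and such a patient can qualify on any other one.
- The 9-point figure for systemic reactions is one reading only. The rule is worded for four dimensions and does not say that the percentage is taken of each sensation's attainable maximum. The perfect-score consequence is likewise conditional on applying 15 points to sensations with three dimensions.
- It cannot be said that 75% is the intended value, or that 12 points is. With Additional file 2 not shown, the misprint could be the percentage, the points or the number of dimensions.
- The cut-off does not enter the primary comparison, the sample size or eligibility, and the economic evaluation is triggered by treatment response, not by sensation score.

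None of this reconciles the two halves of the rule. Nor is this a detail left to a fuller document: the article states the threshold itself.

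**Conclusion.** The threshold is wrong as written: on the described scale 60% is 12 of 20 and 15 points is 75%. Applied literally to the three systemic reactions, 15 points is 100% of what they can score. This rests only on the article's own description of four dimensions scored 0 to 5.

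The effect is limited to one exploratory subgroup analysis with a prespecified direction. The patients affected are those who meet the 60% cut-off on some sensation and 15 points on none. How many they are cannot be derived: the article reports reliability and factor loadings from a 64-patient test of the scale, but no distribution of scores. The primary outcome and the sample size are unaffected.

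**What to change.** Before database lock, check the scale in Additional file 2 and state one cut-off that agrees as a percentage and as points:
- if 60% is meant, 12 of 20;
- if 15 of 20 is meant, 75%;
- if the description of the dimensions is wrong, the corrected scale maximum and the cut-off that follows from it.

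Also state how the rule applies to the three systemic reactions, for example as the same percentage of their attainable maximum of 15 (9 points at 60%).

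The cost is a line or two of text. No new data are needed, provided the individual dimension scores are recorded.
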